## Abstract

**Purpose:**

Surgery is the main treatment for non-metastatic colorectal cancer. Despite huge improvements in perioperative care, colorectal surgery is still associated with a significant burden of postoperative complications and ultimately costs for healthcare organizations. Systematic clinical auditing activity has already proven to be effective in measuring and improving clinical outcomes, and for this reason, we decided to evaluate its impact in a large area of northern Italy.

**Methods:**

The Emilia-Romagna Surgical Colorectal Audit (ESCA) is an observational, multicentric, retro-prospective study, carried out by 7 hospitals located in the Emilia-Romagna region. All consecutive patients undergoing surgery for colorectal cancer during a 54-month study period will be enrolled. Data regarding baseline conditions, preoperative diagnostic work-up, surgery and postoperative course will be collected in a dedicated case report form. Primary outcomes regard postoperative complications and mortality. Secondary outcomes include each center’s adherence to the auditing (enrolment rate) and evaluation of the systematic feedback activity on key performance indicators for the entire perioperative process.

**Conclusion:**

This protocol describes the methodology of the Emilia-Romagna Surgical Colorectal Audit. The study will provide real-world clinical data essential for benchmarking and feedback activity, to positively impact outcomes and ultimately to improve the entire healthcare process of patients undergoing colorectal cancer surgery.

**Clinical trial registration:**

The study ESCA is registered on the clinicaltrials.gov platform (Identifier: NCT03982641).

**Supplementary Information:**

The online version contains supplementary material available at 10.1007/s00384-022-04203-w.

## Introduction

*“If you can not measure it, you can not improve it” (Lord Kelvin)*

A clinical audit is a process which assesses whether healthcare is meeting standards, with the capacity to reduce care disparities as well as being a method to cut unnecessary costs. Where indicated, changes are implemented at an individual, team, or service level, and further monitoring is used to confirm improvement in healthcare delivery [1]. Reliable data, meticulous measurement, and systematic feedback to participants about their performances are the three pillars at the base of an effective clinical audit. Only good data can bring understanding of what does and does not improve the quality of healthcare, and a continuous assessment process allows for concrete advancement (Fig. 1).

**Fig. 1 Fig1:**
[figure not shown]
General and ESCA clinical auditing process

The so-called “Hawthorne effect” (the awareness of being monitored positively influences the behavior of monitored individuals) also helps improve the process, as already widely demonstrated [2–6].

Medical literature offers a vast number of international clinical audits focused on colorectal cancer surgery [7–10]. The Dutch Colorectal Audit (DCRA) probably represents one of the most effective initiatives aiming at improving surgical quality outcomes [7]. DCRA started in 2009 and after just 8 years of activity more than 70,000 patients were included, showing a dramatic decrease in postoperative mortality from 3.4 to 1.8% for colon cancer and from 2.3 to 1% for rectal cancer [10]. Moreover, a significant reduction in costs for the entire healthcare system was observed along with a reduction in complications [11] and an optimization of resources such as the reduction in preoperative radiation therapy for rectal cancer without any impact on oncological outcomes[12].

In 2020, more than 43,000 people in Italy were diagnosed with colorectal cancer (CRC). Of these, approximately 800 of them lived in proximity of the centers taking part in this study [13]. Looking at the administrative data of the Emilia-Romagna region, huge variability was also observed in terms of volume and surgical outcomes, ranging respectively from 36 to 290 procedures per hospital and 2.26% up to 9.45% for 30-day mortality [14].

Following the path of the DCRA experience and given the heterogeneity of surgical outcomes among the hospitals in our region, we decided for the first time in Italy to promote a systematic clinical auditing pilot study focused on CRC surgical care and its possible benefit on outcomes.

## Methods

### Data governance and ethics

The protocol has been described according to the Standard Protocol Items: Recommendation for the Investigational Trials (SPIRIT) checklist [15] (Appendix). The ethical committee approved the project for each of the centers taking part according to local regulations, and it has been registered on the clinicaltrials.gov platform (Identifier: NCT03982641). The Romagna Ethical Committee (CEROM) approval number is 2278.

### Study organization, administration, and governance

The Emilia-Romagna Surgical Colorectal Audit (ESCA) is a multicenter, retro-prospective, observational non-profit study promoted by the IRCCS Istituto Romagnolo per lo Studio dei Tumori (IRST) “Dino Amadori” in Meldola and the Local Health Agency of Romagna (AUSL Romagna).

Members of the surgical units participating in the study contributed to its design gave feedback and reviewed the study protocol. ESCA is overseen by a study steering committee composed of surgeons, epidemiologists, statisticians, IT specialists, and healthcare administrators.

ESCA received a financial support from Johnson & Johnson Medical S.p.a Ethicon Division for data management and monitoring.

The objectives of the study are as follows:To systematically collect data of all patients undergoing surgical treatment for primary CRC from diagnosis up to 6 months after surgery;To evaluate risk adjusted post-operative complications and mortality;To evaluate adherence to the clinical audit activity of each participating center;To evaluate the possible positive effects on outcomes, both clinical and economic, of systematic measurement and monitoring (Hawthorne effect).

### Setting and study population

Patients will be enrolled from the 7 hospitals located in the Emilia-Romagna region in Northern Italy (Table 1), during a 54-month study period. The recruitment target is around 800 patients per year on the basis of demographic data reported in previous years.

**Table 1 Tab1:** Participating centers

Participating centers
Hospital “Degli Infermi” — Faenza
Hospital “S.Maria delle Croci” — Ravenna
Hospital “Morgagni-Pierantoni” — Forlì
Hospital “Infermi” — Rimini
Hospital “Bufalini” — Cesena
Hospital “Ceccarini” — Riccione
Hospital “Giovanni da Saliceto” — Piacenza

### Inclusion criteria

All consecutive patients undergoing surgery for primary CRC between 15 April 2019 and 31 December 2023 will be enrolled in the study. All types of surgical procedures are included, irrespective of setting (urgent/emergent or elective), intent (curative or palliative), and approach (open or minimally invasive). Eligible patients are asked to sign an informed consent form. Cognitive impairment is not considered an exclusion criterion if informed consent is obtained by an appropriate healthcare proxy.

### Exclusion criteria

Patients with multiple synchronous primary tumors are excluded from the analysis. Patients who are unwilling to sign an informed consent form are also excluded.

### Patient’s withdrawal

Participating subjects have the right to withdraw at any time for any reason; data will be collected until the patient’s withdrawal point.

### Study outcomes

The primary objective of this analysis is to assess the frequency of post-operative complications, unplanned re-interventions, re-admissions, and mortality rates (at 30, 90, and 180 days after surgery).

Secondary outcomes include adherence to the clinical audit by each center (intended as the percentage of enrolled eligible patients) along with the study timeframe and possible positive effects on outcomes, both clinical and economic, of systematic measurement and monitoring.

### Key performance indicators, case-mix, benchmarking, and feed-back activity

A core set of key performance indicators (KPIs) will be assessed to measure performance and evaluate the quality of colorectal cancer surgery across the participating centers (Table 2). Each KPI will be estimated both as unadjusted and risk adjusted for differences in patients’ characteristics for a fair comparison among the participating hospitals.

**Table 2 Tab2:** Overview of the selected key performance indicators

**ID**	**Indicator title**	**Indicator description**	**Indicator type**
1	Multidisciplinary discussion	Rate of patients discussed at a multidisciplinary meeting (MDM) before surgery	Colon and rectal cancer
2	Neoadjuvant treatment	Rate of patients receiving neoadjuvant treatment (radiation therapy, chemo-radiation, chemotherapy, total neoadjuvant treatment)	Rectal cancer
3	Minimally invasive resections	Rate of patients undergoing minimally invasive resection	Colon and rectal cancer
4	Conversion	Conversion rate from minimally invasive to open surgery at any time during the procedure	Colon and rectal cancer
5	Anastomotic leak	Rate of anastomotic leakage	Colon and rectal cancer
6	Anastomosis	Rate of patients undergoing anastomosis after low anterior resection	Rectal cancer
7	Loop ileostomy	Rate of loop ileostomy creation after low anterior resection	Rectal cancer
8	Length of stay (LOS)	Rate of patients discharged within postoperative days 3 and 5	Colon and rectal cancer
9	Postoperative complications	Rate of patients with severe postoperative complications (grade ≥ 3 according to Clavien–Dindo classification)	Colon and rectal cancer
10	Quality of total mesorectal excision (TME)	Rate of patients with TME grade 1 or 2	Rectal cancer
11	Positive circumferential resection margins (CRM)	Rate of reported positive CRMs (less than or equal to 1 mm)	Rectal cancer
12	Lymph-nodes yield	Rate of patients for who received adequate lymphadenectomy (≥ 12 lymph-nodes)	Colon and rectal cancer
13	Unplanned reintervention	Rate of patients with an unplanned return to theatre within 30 days after index surgery	Colon and rectal cancer
14	Unplanned readmission	Rate of patients with unplanned readmission within 30 days after discharge/transfer from surgical unit	Colon and rectal cancer
15	Postoperative mortality	Rate of patients who died 30,90, or 180 days after surgery	Colon and rectal cancer

Every 12 months, an anonymized report on volume and KPIs will be delivered to each hospital comparing data of all the participating centers. A set of relevant case-mix variables (patients’ frailty, tumor burden, type of surgery) will be also identified in order to produce a reliable comparison of outcomes between hospitals and give each center case-mix adjusted outcomes.

Data collected during the first 18 months (from April 2019 to October 2020) will be analyzed in order to evaluate preliminary results on primary and secondary outcomes. The first preliminary analysis will be used as benchmark to further implement the auditing activity.

Case-mix adjusted data will be presented using funnel plots with a 95% confidence interval (Fig. 2).

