#### Surgery

Type of surgical procedure, regimen, length of surgery, and operative technique is collected. Possible intraoperative complications are identified and specified as well as the need for intraoperative blood transfusions. The radicality of surgery is assessed as well as type of anastomosis including characteristics and technique. If stoma is created, details are reported as appropriate. All surgical items are reported in detail in Table 5.

**Table 5 Tab5:** Surgical variables

SURGERY	POSSIBLE ANSWERS
Colonic stent preoperatively placed?	yes/no
Surgical regimen	Elective Urgent Unknown
Surgical intent	Curative Palliative Unknown
Surgical technique	Laparotomy Laparoscopy Robotic TEM Transanal open TAMIS taTME Unknown
Conversion	yes/no
Time to conversion	Early (< 60 minutes) Late (> 60 minutes)
Reason of conversion	Reactive Strategic
Surgical procedure	Ileo-cecal resection Right colectomy Extended right colectomy Transverse colon resection Splenic flexure resection Left colectomy Low anterior resection with PME Sigmoid resection Subtotal colectomy Abdomino-perineal excision Total proctocolectomy Transanal local excision Explorative procedure
Type of abdomino-perineal resection:	Standard APR (APE) Extralevator APR (ELAPE) Pelvic exenteration Beyond TME (APR with sacrectomy)
Type of pelvic exenteration: (specify organ included into the resection)	Cystectomy Prostatectomy Istero-annessectomy
Intra-operative complications	yes/no
Type of Intra-operative complication	Splenic injury Biliary injury Small bowel injury Vaginal injury Urological injury Peritoneal perforation during transanal procedure
Additional resections	Ileal resection Minor hepatic resection Major hepatic resection Other abdominal/pelvic organs Peritonectomy (including HIPEC) Lung resection Other (specify)
Intra-operative blood transfusion?	yes/no
Length of surgery	value [minutes]
Radicality	R0/R1/R2
Anastomosis	yes/no
Type of anastomosis—1	Hand-sewn Stapled
Type of anastomosis—2	Ileo-colonic Colo-colonic Colo-rectal Ileo-rectal Colo-anal Ileo-anal
Type of anastomosis—3	Intra-corporeal Extra-corporeal Not applicable
Stoma?	yes/no
Type of stoma	End ileostomy End colostomy Loop ileostomy Loop colostomy

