## Statistical considerations

All the analyses will be performed considering tumor location (colon or rectum) as a stratification factor. For continuous variables, the arithmetic mean and standard deviation (SD), as well as the median value and minimum–maximum, will be presented. Absolute frequencies together with the percentage relative frequencies will be reported while summarizing qualitative variables.

To evaluate the performance of surgical activity, absolute numbers and relative percentages of each performance indicator reported will be calculated. The mortality rate will be defined as the number of patients who died within 30, 90, and 180 days after surgery. Graphical representation will also be used: funnel plots will be displayed for each KPI, both in unadjusted and adjusted versions.

Appropriate statistical models (i.e., mixed models, logistical regression, multilevel models) will be developed to evaluate the relationship among analyzed indicators and potential explanatory factors as well as for standardization/adjustment purposes. Main covariates will include age, gender, ASA score, CCI, surgery setting (urgent vs. elective), and ECOG.

Hospitals will be used as random effects to account for the presence of possible variability among hospitals. Other exploratory subgroup analyses will be performed.

Furthermore, to assess the effects of continuous monitoring and benchmarking on clinical outcomes, a before-and-after approach will be used. Specifically, assuming the time from the first subject surgery until the release of the first benchmarking report as the reference period (baseline, i.e., “before” period), the analysis will evaluate any significant changes occurred afterwards. Any changes on the outcomes will be, therefore, attributed to the benchmarking effect.

Missing values will be replaced and estimated using multiple imputations. A two-sided 95% confidence interval (95% CI) will be reported as appropriate.

Statistical analysis will be performed using R statistical software (v. 4.0.6) — www.r-project.org.

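### KPI 7 (loop ileostomy) is set on all low anterior resections, so its hospital comparison partly reflects how many patients were given an anastomosis

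*Protocol article*

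**What the plan says.** Table 2 of the protocol article (section on key performance indicators, case-mix, benchmarking and feedback) describes KPI 7, for rectal cancer, as "Rate of loop ileostomy creation after low anterior resection". The row above, KPI 6, is "Rate of patients undergoing anastomosis after low anterior resection". No section gives another denominator for KPI 7.

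Table 5 (Surgery) lists "Low anterior resection with PME" as a procedure and has no separate category for a low anterior resection without an anastomosis. It records anastomosis as its own yes/no item. Stoma types are coded "End ileostomy End colostomy Loop ileostomy Loop colostomy".

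On use, the KPI section says "Each KPI will be estimated both as unadjusted and risk adjusted for differences in" patient characteristics, so that hospitals can be compared fairly, and reports go to hospitals every 12 months. Statistical considerations adds that "funnel plots will be displayed for each KPI, both in unadjusted and adjusted versions". On adjustment, that section states "Main covariates will include age, gender, ASA score, CCI, surgery setting (urgent vs. elective), and ECOG". The KPI section names frailty, "tumor burden, type of surgery" as case-mix variables. Neither list names anastomosis.

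**The concern.** KPI 6 carries information only if some low anterior resections end without an anastomosis; otherwise it would be 100% everywhere. Because KPI 7 uses the same population phrase, those patients also sit in its denominator. A loop ileostomy is ordinarily made to divert above a join, so a patient without one is unlikely to count as an event. KPI 7 would then fall when a hospital joins fewer patients, even if it diverts exactly the same share of those it joins.

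What is at stake is how the benchmarking report is read. A hospital could appear as a low user of loop ileostomy when its only difference from the others is its anastomosis rate, which KPI 6 already reports. The named adjustment variables describe the patient, the tumour and the operation. None of them is the anastomosis decision, so the adjusted funnel plot need not remove the effect.

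**Working it through.** The article states no value for KPI 6 or KPI 7, so there is no figure to reproduce. The check is an identity with assumed inputs.

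**Identity.** Let *a* be the share of low anterior resections with an anastomosis (KPI 6), *q* the loop-ileostomy rate among those with one, and *r* the rate among those without. Then

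KPI 7 as written = *a*·*q* + (1 − *a*)·*r*.

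This is free of *a* only if *r* = *q*. For any *r* below *q*, it falls as *a* falls.

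**Inputs.** The denominators come from Table 2. All rates and volumes below are assumptions.

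**Size with *r* = 0:**

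| *q* | *a* = 1.00 | 0.95 | 0.80 | 0.70 | 0.60 |
|---|---|---|---|---|---|
| 0.40 | 40% | 38% | 32% | 28% | 24% |
| 0.60 | 60% | 57% | 48% | 42% | 36% |
| 0.80 | 80% | 76% | 64% | 56% | 48% |

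At *q* = 0.60, going from *a* = 0.95 to 0.70 moves KPI 7 by 57 − 42 = 15 points with no difference in diversion among joined patients.

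**Sensitivity to *r* (*q* = 0.60, *a* = 0.95 against 0.70):**
- *r* = 0.05: 57.3% against 43.5%.
- *r* = 0.10: 57.5% against 45.0%.
- *r* = 0.60: 60% in both.

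**Order can reverse (*r* = 0).** A hospital with *a* = 0.95 and *q* = 0.55 shows 0.95 × 0.55 = 52.3%. One with *a* = 0.70 and *q* = 0.70 shows 0.70 × 0.70 = 49.0%. The hospital that diverts more of its joins looks lower.

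**Chance of a low flag.** Take *q* = 0.60 everywhere, *r* = 0 and an average *a* of 0.90, so the funnel is centred at 0.90 × 0.60 = 0.54. A hospital with *a* = 0.75 expects 0.75 × 0.60 = 0.45. The lower limit is 0.54 − 1.96·√(0.54 × 0.46/*n*), and the probabilities are exact binomial.

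| *n* | Lower limit | Flagged if events ≤ | P at 0.45 | P at 0.54 |
|---|---|---|---|---|
| 20 | 0.322 | 6 | 0.13 | 0.03 |
| 60 | 0.414 | 24 | 0.26 | 0.02 |
| 90 | 0.437 | 39 | 0.42 | 0.03 |

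About 20 resections a year over the stated 54 months gives 20 × 4.5 = 90. The *n* = 20 row therefore matches one annual report and the *n* = 90 row the whole study pooled.

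**Same scenario on KPI 6.** The funnel is centred at 0.90 and the hospital is at 0.75. The chance of falling below the lower limit is 0.59 at *n* = 20, 0.91 at *n* = 60 and 0.98 at *n* = 90.

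**With the denominator limited to joined patients.** The indicator equals *q*. The two hospitals at 57% and 42% both show 60%.

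**The case against.** **The all-resection rate is legitimate.** The share of all low anterior resections that receive a loop ileostomy is a well-defined process rate and parallels KPI 6. The article never says that KPI 7 measures diversion among joined patients. This stands: KPI 7 is not wrong as a descriptive figure. The point concerns its use for comparing hospitals.

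**Table 2 is an overview.** KPI 5, anastomotic leakage, also leaves its restriction to patients with an anastomosis unsaid, and exact filters may sit in the full protocol. This stands in part. KPI 7 does name its population, however, and nothing in the article narrows it.

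**A patient without a join cannot have the event.** A reader might infer this, and that KPI 7 equals KPI 6 times the diversion rate exactly. The article does not support it, because Table 5 does not tie stoma type to anastomosis status. Only the weaker assumption *r* < *q* is needed for the direction.

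**KPI 6 sits beside it.** In the scenario above KPI 6 would flag the true cause more often than KPI 7 raises a misleading flag, and the crude conditional rate can be recovered as KPI 7/KPI 6 if *r* = 0. This stands and lowers the importance. That division does not undo the adjusted funnel plot.

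**The adjustment set is open.** The covariates are described as the main ones, and type of surgery is among the case-mix variables. Neither amounts to adjusting for anastomosis.

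**Before-and-after analysis.** A reader might infer that a shift in the share of patients joined would be credited to benchmarking through KPI 7. Statistical considerations applies that comparison to clinical outcomes, and no section says that KPI 7, a process indicator, enters it. The inference holds only if KPI 7 is included.

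**Conclusion.** The point holds as a minor weakness in the definition of one indicator. As worded, KPI 7 shares KPI 6's population, so its hospital comparison combines two decisions, and no named adjustment variable separates them. The direction rests on one assumption outside the article: that loop ileostomies are less frequent without an anastomosis than with one.

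The size is illustrative only. The 15-point spread depends on the assumed diversion and anastomosis rates. For an annual report the misleading low flag is a modest risk, and the larger probability applies only to data pooled over the whole study. KPI 7 is one of 15 indicators, is not a primary outcome and has no stated threshold or preferred direction. Nothing here bears on which operation or stoma policy is right.

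**What to change.** For benchmarking, define KPI 7 as the loop-ileostomy rate among low anterior resections with an anastomosis, and use that denominator in the unadjusted and adjusted funnel plots. Keep KPI 6 on all low anterior resections. If the all-resection loop-ileostomy rate is also wanted, show it as a descriptive figure to be read with KPI 6. If KPI 7 is to enter the before-and-after comparison, use the restricted denominator there too.

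The cost is one line in Table 2 and a filter on the anastomosis yes/no item in Table 5, which can be applied to data already entered. The denominator shrinks and the limits widen slightly. With 20 resections and 90% joined, the half-width goes from 1.96·√(0.54 × 0.46/20) = 21.8 points to 1.96·√(0.60 × 0.40/18) = 22.6 points. Some influence of which patients each hospital chooses to join remains, because joined patients may differ in risk between hospitals; the report should say so.

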**Fig. 2 Fig2:**
[figure not shown]
Case-mix adjusted data will be presented using funnel plots with a 95% confidence interval

Reports of the enrolment rate, obtained by comparing the number of enrolled patients to the hospital discharge cards (HDC), will be sent to each center every 3 months. The aim of this feedback activity is to progressively obtain a 100% enrolment of eligible patients and thus provide “real-world data” that avoid bias related to patient selection.

